## Trial size estimates for the primary hypotheses

### Hypothesis A

The outcome in this hypothesis is severe illness in the first 14 weeks of life. Based on an estimated 10% risk of severe illness in the first 14 weeks of life [65], 90% power and a risk ratio of 0.7, the required sample size is 1914 (Table 1).

**Table 1 Tab1:** Assumptions used for sample size calculation for the first 14 weeks of life

Assumption	Estimated level
Two-sided significance level	0.05
Ratio of sample size early/late BCG vaccination	1
Percent of vaccinated at 14 weeks of age with severe illness	15
Percent of vaccinated at birth with severe illness	10
Risk ratio:	0.7
Risk difference	5
Total sample size (i.e., in both trial arms)	1914

*BCG* Bacillus Calmette-Guérin

Taking into account 10% attrition and that up to 5% of the infants may have contracted HIV-1 infection when enrolled, a total of 2200 babies are required for this trial, 1100 children in each study arm.

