## Randomization

Infants of HIV-1-infected mothers are randomized within 24 h of birth using pre-prepared randomization lists. Randomization is stratified by clinic using permuted blocks of varying size (4, 6 or 8). Eligible infants are allocated in a 1:1 ratio to one of the two following arms: BCG vaccination within 24 h of birth or BCG vaccination at week 14. All computer-generated randomization lists were prepared for each clinic by an independent scientist, and are kept safely off site. Concealment until the mother-infant pair has been deemed eligible for final inclusion is ensured using an application running on a dedicated Android cell phone at each clinic.

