## Follow-up and subject retention

Follow-up visits at the study clinic are scheduled on day 7 and at weeks 2, 6, 10, 14, 15, 26, 28, 48 and 52 after birth (Figs. 2 and 3). At each of these visits, data is collected on the primary and secondary study outcomes, adverse events (localized abscess formation, suppurative lymphadenitis and disseminated BCG infection), anthropometry and on potential confounding variables (see above). Mothers are given a cell phone to facilitate contact with study staff in case of an illness or other important child events.

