Also, autoregressive correlation approaches will be used to account for multiple and possibly correlated observations within the same study participant. These methods take the correlation structures into account and thereby the fact that measurements taken closer in time for an individual are likely to be more correlated than two measurements taken farther apart for that same individual. Efficacy will be calculated as 100 × (1 − RR), 100 × (1 − IRR) or 100 × (1 − HR). The prevalence of BCG scarring will be compared between the two study arms using the abovementioned approaches, as appropriate. Linear regression and or *t* tests will be used to compare the TNF and IFN-γ responses between the trial arms. We will consider adjusting for potential confounders if: (1) there are baseline imbalances between trial arms, (2) the variables for which there are such baseline differences are strongly associated with the study event or (3) they cause a ≥5% difference in the effect measures when they are added to the main model. Full case analyses will be default, but appropriate imputations will be considered for missing data.

In addition to the *intention-to-treat analysis*, where outcomes will be compared according to the random allocation, *instrumental variable analyses* will be conducted in an attempt to estimate biological/causal effects of the actual receipt of the vaccine. In these analyses, random allocation will be the instrument. To enable such analyses, actual receipt as well as the age of BCG vaccination will be captured in all participants. We will also perform *per-protocol* and *as-treated* analyses.

The primary analyses will include all HIV-1-exposed infants, adjusting for any imbalance in HIV-1 status between the two trial arms, as appropriate. However, we will also perform an analysis of the large subgroup of babies who remain uninfected with HIV-1.

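### Covariates may enter the primary comparison after the data are seen, and the stated analysis makes no provision for clinic, the stratification factor; the expected harm is modest

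*Protocol article*

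**What the plan says.** All references are to the protocol article.

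- **Randomization:** "Randomization is stratified by clinic using permuted blocks of varying size (4, 6 or 8". There are three clinics. Infants are randomised within 24 h of birth.
- **Plan of analysis, Primary analysis and Secondary analysis:** the named methods are chi-square and t tests, log-binomial, logistic, Poisson or negative binomial regression, GEE and Cox models. None is said to include clinic. The only correlation structure described is within child. Clinic is also absent from the variables listed under the heading on baseline features and potential confounders.
- **Primary analysis, covariates:** "We will consider adjusting for potential confounders if: (1) there are baseline imbalances between trial arms". Trigger (2) is that the imbalanced variables are strongly associated with the event. Trigger (3) is a change of at least 5% in the effect measure when they are added. The triggers are joined by 'or'. Complete-case analysis is the default.
- **Primary analysis, HIV-1:** the primary analyses cover all exposed infants, "adjusting for any imbalance in HIV-1 status between the two trial arms, as appropriate". No time point for that status is given. There is in addition "an analysis of the large subgroup of babies who remain uninfected with HIV-1".
- **Timing of HIV-1 information:** Postnatal screening has blood drawn at birth for PCR. Ethical considerations has a PCR diagnosis at 6 weeks of age and acknowledges transmission through breast milk in the first months.
- **Blinding/masking:** the trial is open-label, with outcome recorders blinded as far as possible.

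**The concern.** In a randomised trial, baseline imbalance is chance. A rule that picks covariates by observed imbalance, or by how far they move the treatment estimate, makes the final model a function of the data. The article sets no imbalance threshold, no list of eligible covariates for this purpose and no statement of whether the adjusted or the unadjusted result leads. The Secondary analysis section applies the opposite standard to subgroups, which are to be set beforehand from the literature and not by study data.

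Clinic is more than a silent omission. The article states when adjustment will be considered, and stratified blocks keep clinic balanced. Triggers (1) and (2) would therefore not bring it in, and trigger (3) is unlikely to.

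HIV-1 status is a legitimate covariate if taken at birth. Without a time point it could include infection acquired after BCG was given or withheld, and remaining uninfected is information from follow-up.

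At stake are the credibility of the lead estimate, a small type I error inflation if models can be chosen between, and some precision.

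**Working it through.** **1. The plan's own figure.** Inputs come from Table 1 under Hypothesis A. "Two-sided significance level" is 0.05, "Percent of vaccinated at 14 weeks of age with severe illness" is 15, and the corresponding figure for BCG at birth is 10. The text gives "90% power and a risk ratio of 0.7, the required sample size is 1914".

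Per arm, n = [1.960·√(2·0.125·0.875) + 1.282·√(0.15·0.85 + 0.10·0.90)]² / 0.05² = (0.9167 + 0.5977)² / 0.0025 = 917.3.

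With continuity correction, n′ = (n/4)·[1 + √(1 + 4/(n·0.05))]² = 956.9, so 957 per arm and 1914 in total. The figure reproduces from the tabulated risks. It uses no covariates, so changing the adjustment rule does not change 1914 or 2200.

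**2. Ignoring clinic.** Simulation at N = 1914 with 20,000 runs per scenario. Assumptions: three equal clinics, delayed-arm risks as shown, and a risk ratio of 2/3 under the alternative.

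| Clinic risks (%) | Type I, pooled | Type I, stratified | Power, pooled | Power, stratified |
|---|---|---|---|---|
| 15/15/15 | 0.050 | 0.050 | 0.914 | 0.914 |
| 10/15/20 | 0.049 | 0.051 | 0.916 | 0.917 |
| 5/15/25 | 0.041 | 0.048 | 0.920 | 0.927 |

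The mismatch with the design is on the safe side. The largest power loss is 0.927 − 0.920, under 1 point.

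**3. Data-driven covariates, severe illness.** Simulation at N = 1914 with ten independent baseline covariates, each nominally explaining 0.5% or 1% of the variance. The model was a linear probability model with robust standard errors, with 4,000 null runs.

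| Result reported | Type I, 0.5% each | Type I, 1% each |
|---|---|---|
| Unadjusted | 0.047 | 0.046 |
| Adjusted if imbalanced at p<0.05 | 0.048 | 0.043 |
| Adjusted if effect moves ≥5% | 0.048 | 0.047 |
| All ten, prespecified | 0.048 | 0.050 |
| Best of the first three | 0.055 | 0.063 |

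The Monte Carlo standard error is √(0.05·0.95/4000) = 0.0034. Each rule applied mechanically holds its level. Only free choice among the results raises it.

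A second simulation (n = 2200, 2,500 runs, better of two results) gave 5.2% against 4.8% unadjusted. With a standard error of 0.44 points, that 5.2% cannot be told apart from 5%.

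Under the planned effect with 1% each (2,000 runs), power was 0.78 unadjusted, 0.79 with the imbalance rule, 0.80 with the 5% rule and 0.83 prespecified. These levels lie below the planned 90% because simulated risks were truncated near zero, which shrinks the contrast to about 15.5% against 11.2%. Only the differences between rows are informative.

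**4. How often trigger (3) fires.** On the risk-difference scale it is erratic. It selected 5.8 to 6.6 of ten covariates on average under no effect, and about 1.8 under the planned effect, because 5% of a near-zero difference is tiny.

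On the ratio scale at 2200 infants it is nearly inert. The chance imbalance in a standardised covariate has SD √(4/2200) = 0.0426. A covariate with risk ratio 1.3 per SD then shifts the log risk ratio by ln(1.3)·0.0426 = 0.011 (one SD). A 5% change needs ln(1.05) = 0.049, which is 4.4 SDs. At 1.49 per SD the shift is 0.017, so 2.9 SDs are needed. That gives about 0.3% per covariate and about 3% for at least one of ten.

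**5. Cytokines, 50 per arm.** Simulation with 6,000 runs and an assumed SD of 0.8 on the log scale gave 5.2% unadjusted, 5.1% prespecified and 7.1% when the better of adjusted and unadjusted is reported (standard error 0.28 points). The figure depends on assumed covariate strengths, which the protocol does not give. Treat it as indicative.

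**The case against.** The best reply is that this is a condensed article. It never excludes clinic, it refers to a detailed analysis plan (for subgroups), and stratum terms are commonly left to such a plan. The adjustment wording is also permissive, covariates are added to a main model that exists first, and each rule applied mechanically keeps its level. Most of this stands, and it limits the size of the point. It does not remove it: the adjustment rule is written out, so a later plan would have to replace it and not merely complete it.

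Four stronger readings are tempting, and the documents do not support them.

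- **That ignoring clinic undermines the primary test.** The error is conservative and small.
- **That the primary model would usually turn on chance imbalance.** With about 20 listed variables, 1 − 0.95^20 = 64% would show at least one imbalance at p<0.05. This assumes independence and a p-value criterion. The article sets no such criterion, and several items are plainly related, such as income with employment, or CD4 count with viral load.
- **That confounders measured at follow-up enter the model.** Visits do collect "anthropometry and on potential confounding variables (see above", but the first two triggers speak of baseline differences.
- **That HIV-1 adjustment breaks the randomised comparison.** That would need BCG timing to affect HIV-1 acquisition, which nothing here shows. Blood is drawn at birth, the sample-size text speaks of infection at enrolment, and infection at 6 weeks is put below 3.5%. The uninfected analysis is additional to the primary one. What remains is an unfixed time point.

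**Conclusion.** The point holds in a limited form. The primary comparison has a stated, data-driven adjustment rule with three alternative triggers, and the stated analysis makes no provision for the factor used to stratify randomisation. It should be changed, but it does not threaten the trial.

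Omitting clinic costs under 1 point of power and errs on the conservative side, with three equal clinics and risks no more spread than 5% to 25%. Type I error reaches roughly 5–6% for severe illness, and perhaps 7% for the cytokine comparison, only if someone may choose among models after seeing results. The article does not say this will happen, but it does not prevent it. These figures rest on assumed covariate strengths. The main benefit of a fixed model is that the lead result is known in advance, with some gain in precision (0.78 to 0.83 in power in one favourable scenario). The HIV-1 element is a matter of stating the time point and labelling the subgroup correctly.

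**What to change.** 1. Delete triggers (1) to (3).
2. Name one primary model per co-primary outcome. Include clinic, as a model term or a Mantel-Haenszel stratum, and a short fixed list of baseline covariates already collected, such as birth weight and sex. Use them whatever the observed imbalance.
3. Add maternal CD4 count only with a stated way to keep infants whose mother has no value. The test is only offered at antenatal screening, and under the complete-case default it could drop randomised infants.
4. If HIV-1 status is adjusted for, use only the PCR on blood drawn at birth. Define the uninfected subgroup by that sample, or label the analysis of infants who stay uninfected as conditioning on a post-randomisation variable.

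The cost is analysis wording only, with no new data and no change to 1914 or 2200. The analysts lose the freedom to add covariates later. A subgroup defined at birth would contain a few infants infected during or after birth.

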### Secondary analysis

Risk of severe illness from 48 h after randomization until the first 14 weeks of life, after the 14 weeks of infancy and during the entire infancy period will be analyzed as described above for the primary analysisAs a hypothesis-generating effort to understand the latency period after which BCG may induce NSEs, we will calculate the protection against severe illness during the first 14 weeks of life on a sliding scale starting from randomization until seven completed days post randomizationRisk of child death in the first 14 weeks as well as in the remaining 38 weeks of infancy: time-to-event analysis will be used to estimate time to severe illness or death. Kaplan-Meier methods and log-rank tests will be used for descriptive analyses. The results from these analyses will be presented as Kaplan-Meier probabilities of the endpoints by a specified time for every 1000 children. Cox proportional hazards regression models will be used to estimate the effect of the intervention on child death. For this outcome, data will be censored when a child is lost to follow-upRisk of clinical sepsis and of “confirmed sepsis” in the first 14 as well as in the remaining 38 weeks of infancySafety will be analyzed according to type, frequency and severity of adverse events (AEs) that occur in children during the trialSubgroup analysis for potential effect measure modification will be on the strata defined by maternal CD4 counts (<350 or ≥350 cells/μL), low birth weight (<2500 or ≥2500 g) and the babies’ HIV status, sex of the child, in addition to other baseline characteristics which we have reasons to believe may interact with delayed BCG administration. Such subgroup/interaction analyses will be defined based on the available scientific literature before embarking on the analyses, will not be driven by study data, and will be described in a detailed analysis planSurvival analyses using nonparametric and parametric methods to extrapolate over 5 years the incidence of NSEs and death for use in economic evaluation

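### The exploratory latency analysis moves only the start of the 14-week window, by 0 to 7 days, so it has little ability to show an onset of protection within week 1 and cannot locate a later one

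*Protocol article*

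**What the plan says.** The protocol article, under Secondary analysis, describes the item as a "hypothesis-generating effort to understand the latency period after which BCG may induce NSEs". The method follows directly: "we will calculate the protection against severe illness during the first 14 weeks of life on a sliding scale starting from randomization", the last start being seven completed days later. The outcome is "protection against severe illness during the first 14 weeks of life", so the end of the window is fixed and only its start moves. No start after day 7 is named, and no arm effect by period is described for this purpose.

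Three nearby statements matter.

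- Under Randomization: "Infants of HIV-1-infected mothers are randomized within 24 h of birth using pre-prepared randomization lists". Time since randomization is therefore close to age, and the full window is about 98 days.
- Another secondary analysis covers "Risk of severe illness from 48 h after randomization until the first 14 weeks of life". That start lies inside the same 0 to 7 day range.
- Under the child-death item: "time-to-event analysis will be used to estimate time to severe illness or death". Kaplan-Meier and log-rank methods are named there for descriptive use and are not linked to latency.

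**The concern.** The aim is to learn when protection begins. Each estimate in the planned series averages the arm effect from its start day to week 14, and every one contains days 7 to 98. The series can differ only through what happens in the first week, which is a small part of follow-up and possibly a small part of the events.

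Two consequences follow. First, an onset within the week shows up as a slight drift between highly correlated estimates. Second, an onset after two, four or six weeks leaves no mark inside the range by which its timing could be read. The document gives no reason to expect a latency under a week, and its cytokine outcomes are measured at 1, 14, 15 and 28 weeks.

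What is at stake is the usefulness of one exploratory analysis, and the risk that its output suggests a latency the data cannot support.

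**Working it through.** **Inputs from the document (Hypothesis A and Table 1).** "Percent of vaccinated at 14 weeks of age with severe illness": 15. "Percent of vaccinated at birth with severe illness": 10. Two-sided alpha 0.05, power 90%, total 1914. The protocol gives no figure for the latency analysis itself.

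**Reproducing the plan's sample size.** For 15% against 10%, the normal-approximation formula gives 918 per arm (1836 in total) without continuity correction. With it, the result is 957 per arm, 1914 in total, which matches. I therefore use 957 per arm and the Table 1 ratio 10/15 = 0.667.

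**Assumptions that are mine.** Before the latency of L days the arms have equal risk; afterwards the risk ratio is 2/3. The document does not give the timing of events, so I show two cases: events spread evenly over 98 days, and front-loaded events (exponential with a 28-day scale, 23% of delayed-arm events in week 1).

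**Overlap.** Days: (98 − 7)/98 = 92.9%. Delayed-arm events: 92.9% if even, 77% if front-loaded. If the daily risk were instead 3 or 6 times higher in week 1, the figures would be 81% or 68%.

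**Shift between start day 0 and start day 7.** Variance of the log risk ratio: V = 1/(events, delayed arm) + 1/(events, birth arm). For nested windows the variance of the difference is V7 − V0. Power = Φ(z − 1.96) + Φ(−z − 1.96), with z = shift/SE.

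Worked case, even events, L = 7:

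- Delayed-arm events: 0.15 × 957 = 143.55 in total, 133.30 from day 7.
- Birth-arm events: 99.12 in total, 88.86 from day 7.
- Risk ratios: 99.12/143.55 = 0.690 and 88.86/133.30 = 0.667. Log shift 0.0351.
- V0 = 0.01706 and V7 = 0.01876. SE of each estimate 0.131 and 0.137; correlation √(V0/V7) = 0.95.
- SE of the shift = √(0.01876 − 0.01706) = 0.041. z = 0.85; power 14%.

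| True latency | Even: RR, start day 0 → day 7 | Power | Front-loaded: RR, start day 0 → day 7 | Power |
|---|---|---|---|---|
| 7 days | 0.690 → 0.667 | 14% | 0.743 → 0.667 | 28% |
| 28 days | 0.762 → 0.744 | 10% | 0.884 → 0.850 | 9% |
| 42 days | 0.810 → 0.795 | 8% | 0.934 → 0.914 | 6% |

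With the 3-fold and 6-fold week 1 risks, power at a 7-day latency is 25% and 33%.

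**Shape of the curve.** With even events and L = 3, the expected risk ratio falls from 0.677 to 0.667 by day 3 and is then flat, so an onset inside the week does leave a bend, though a tiny one. For L = 7, 14, 28 or 42 the curve falls steadily to day 7 without a bend. The length of a longer latency cannot be read from it.

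**What separate periods would give.** Even events, true risk ratio 0.667 throughout, delayed against birth arm:

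- Week 1: 10.25 and 6.84 events. SE = √(1/10.25 + 1/6.84) = 0.494; factor exp(1.96 × 0.494) = 2.63; interval 0.25 to 1.76.
- Weeks 2–4: 31 and 21 events; interval 0.38 to 1.17.
- Weeks 5–14: 103 and 68 events; interval 0.49 to 0.91.

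Power of a 2-df test that the effect differs across these three periods (statistic Σw(b − b̄)², where b is the log risk ratio in a period, w = 1/variance and b̄ is the weighted mean; noncentral chi-square) is 11%, 25% and 16% for latencies of 7, 28 and 42 days with even events, and 22%, 26% and 10% if front-loaded. For example, with L = 28 and even events, b = 0, 0 and −0.405, w = 5.13, 15.38 and 41.01, b̄ = −0.270, so the noncentrality is 20.51 × 0.0731 + 41.01 × 0.0183 = 2.25 and the power 25%.

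**The case against.** The best defence is that the analysis is openly hypothesis-generating and feeds no primary outcome, sample size or stopping rule. The 0 to 7 day range can also be read as an extension of the 48-hour start: how does the estimate change when events too early for BCG to have prevented are left out? Nested windows suit that question. Time-resolved work appears elsewhere too: hazard ratios for severe illness under Primary analysis, Kaplan-Meier curves under the child-death item, and weekly cycles to week 14 in the economic model. Late separation of the arms might therefore be noticed. All of this stands and keeps the point minor. None of it gives an arm effect by period for latency, which is the aim the protocol states.

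A reader might infer more than the document supports:

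- *That the analysis cannot show onset at all.* Differences between nested estimates do carry day-specific information from week 1, and a levelling-off would mark an onset there. The limit is power, not logic.
- *That the estimates are near-identical whatever the timing of illness.* The 93% refers to days. Shared events could be 68 to 81% if illness clusters early, and the drift for a 7-day latency is then visibly larger than for 28 or 42 days.
- *That separate periods solve the problem.* A single contrast cut exactly at the true onset has power of 14%, 32% and 37% (even events; 7, 28 and 42 days), but nobody knows that cut in advance. Six fixed intervals (days 0–1, 2–6, 7–13, 14–27, 28–55, 56–97) with a 5-df test give about 9%, 17% and 15%, which is worse than the sliding start at 7 days and only somewhat better later.
- *That the investigators will read a flat curve as immediate protection.* No such rule is written. It is a risk of interpretation only.

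**Conclusion.** The point holds in limited form and is minor. The planned method does not match its stated aim: it has little ability to show an onset within the first week (power about 14% with even events and 28% with front-loaded events for a 7-day latency, up to 33% with very heavy early clustering), and it cannot locate a latency longer than 7 days. The first statement rests on the Table 1 rates, 957 infants per arm, a step change in effect and assumed event timing. The second follows from the range of start days and does not depend on those rates. The primary comparison is unaffected.

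**What to change.** Keep the sliding start, described as a sensitivity analysis to the exclusion of early events. Beside it, add one model that estimates the arm effect on severe illness in a few prespecified, non-overlapping periods covering all 14 weeks, for example week 1, weeks 2–4 and weeks 5–14, or a smooth time-varying hazard ratio. Plot the difference in cumulative incidence by day. Keep the hypothesis-generating label, and state that a flat sliding curve is not evidence of immediate protection.

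The cost is analysis code and a few sentences; no new data are needed. The intervals will be wide, above all in week 1, and power to detect a change in effect stays at roughly 10 to 25%. At a 7-day latency the three-period test is slightly weaker than the sliding contrast (11% against 14% with even events, 22% against 28% front-loaded), which is a reason to add it and not to replace. The gain is that later onsets come within view.
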